## Abstract

**Background:**

Rapid growth of mobile technologies has resulted in a proliferation of lifestyle-oriented mobile phone apps. However, most do not have a theoretical framework and few have been developed using a community-based participatory research approach. A community academic team will develop a theory-based, culturally tailored, mobile-enabled, Web-based app—the Mobile Cancer Prevention App (mCPA)—to promote adherence to dietary and physical activity guidelines.

**Objective:**

The aim of this study is to develop mCPA content with input from breast cancer survivors.

**Methods:**

Members of SISTAAH (Survivors Involving Supporters to Take Action in Advancing Health) Talk (N=12), treated for Stages I-IIIc breast cancer for less than 1 year, 75 years of age or younger, and English-speaking and writing, will be recruited to participate in the study. To develop the app content, breast cancer survivors will engage with researchers in videotaped and audiotaped sessions, including (1) didactic instructions with goals for, benefits of, and strategies to enhance dietary intake and physical activity, (2) guided discussions for setting individualized goals, monitoring progress, and providing or receiving feedback, (3) experiential nutrition education through cooking demonstrations, and (4) interactive physical activity focused on walking, yoga, and strength training. Qualitative (focus group discussions and key informant interviews) and quantitative (sensory evaluation) methods will be used to evaluate the participatory process and outcomes.

**Results:**

Investigators and participants anticipate development of an acceptable (frequency and duration of usage) feasible (structure, ease of use, features), and accessible mobile app available for intervention testing in early 2017.

**Conclusions:**

Depending on the availability of research funding, mCPA testing, which will be initiated in Miami, will be extended to Chicago, Houston, Philadelphia, and Los Angeles.

## Introduction

For women in the United States, breast cancer is the most common cancer and the second leading cause of cancer death [1]. Although white women have historically had higher incidence rates than African American (AA) women, the rates converged in 2012 [2]. Breast cancer death rates are higher for AA women compared to white women [3]. AA women are more likely to be diagnosed with breast cancer at younger ages and with more aggressive and advanced tumors. Although breast cancer survival in AA women has increased, survival rates remain lower than among white women [4].

Modifiable lifestyle risk factors related to energy balance may contribute to racial/ethnic disparities in breast cancer survival rates. Disparities in these factors are large and persistent, particularly between white and AA women. Recent data from the Behavioral Risk Factor Surveillance System revealed three disparity risk categories for AA women: (1) obesity (35.7% vs 23.7% for whites), (2) inadequate fruit and vegetable consumption (12.6% vs 17.4% for whites), and (3) low physical activity (63.8% vs 50.3% for whites) [5]. Lifestyle behavioral guidance to promote health and prevent disease is a cornerstone of American public health policy, yet relative to women of other races, AA breast cancer survivors are less likely to report adherence to the American Cancer Society [6] and the American Institute for Cancer Research (AICR) [7] cancer prevention guidelines.

Limited research on AAs exists because they have been underrepresented in studies examining health behaviors that improve breast cancer survival. One of the few studies with AA women, the Women’s Healthy Eating and Living Study, showed that at baseline, AA survivors were more likely to be obese (45% vs 25% for whites), to consume more calories from fat (+3.2%), to have fewer servings of fruits (-0.7/day), and were less successful at making and maintaining dietary changes than whites [8]. Greenlee et al [9] completed a randomized controlled trial with the commercially available Curves program, following 42 Hispanic and AA breast cancer survivors (BCSs) for 6 months. The trial resulted in weight loss that was not maintained at 6 months after the intervention. A community-based pilot study of 24 AA BCSs engaged in walking as physical activity (PA) [10] resulted in increases in steps walked per day and decreases in body mass index (BMI), body weight, and waist/hip circumferences, with most changes maintained at 3 months. A pre-post design, that included one of two weekly sessions dedicated to exercise, was used to test a 6-month intervention with 23 AA BCSs [11]. Participants experienced changes in weight, BMI, and social support. In a 16-week home-based motivational exercise program for 13 AA BCSs, there was a post-intervention increase in total minutes of PA and improved physical functioning [12].

To enhance our understanding of health behaviors that improve survival among AA BCSs, a lifestyle needs assessment of 240 members of the support group, SISTAAH (Survivors Involving Supporters to Take Action in Advancing Health) Talk, was completed. Most BCSs reported lack of adherence with cancer prevention recommendations for portion control (89%), body weight (68%), PA (83%), and intake of vegetables/fruits (75%), processed meat (54%), and red meat (53%) [13].

SISTAAH Talk members expressed interest in developing an alternative format for a lifestyle intervention. Rapid expansion of mobile technologies, including smartphone apps, provides such an opportunity. Currently, 85% of American adults own a mobile phone, and 45% own a smartphone, with usage higher among AAs (47%) relative to whites (42%) [14]. Half of all smartphone owners use their phones to search for health information, with 60% of all downloaded health-related apps involving weight loss and exercise [15].

A variety of apps relating to diet, nutrition, and weight control are available from platforms such as iPhone, Android, Nokia, and BlackBerry [16]. Traditional lifestyle interventions are facilitated and resource-intensive and may or may not be evidence-based. mHealth apps are mediated, less expensive, and rarely grounded in theory or evaluated using scientific methods [17-19]. To our knowledge, however, there are no apps that promote adherence to science-based cancer prevention guidelines. Adherence to these guidelines to prevent breast cancer recurrence is the primary focus of the Mobile Cancer Prevention App (mCPA) and such compliance may, in turn, contribute to improving health-related quality of life (eg, physical functioning, depression) [20]. Investigators postulate that employing principles of community-based participatory research (eg, unit of identity, building on resources within the community, cyclical and iterative processes) in developing a smartphone app, will result in widespread use and broader acceptance of cancer prevention guidelines. The purpose of this study is to partner with members of a breast cancer support group to develop a cancer prevention app for subsequent testing in a behavioral intervention study. Investigators hypothesize that a participatory process, one that engages individuals affected *by* the problem in developing solutions *to* the problem [21], will result in an acceptable (frequency and duration of usage), feasible (structure, ease of use, features), and accessible mobile cancer prevention app.

## Methods

### Study Population

Established in 1995 as the first breast cancer support group for women of color in South Florida, the goal of SISTAAH Talk is to provide a forum for African-Americans to communicate about and make sense of their diagnosis and treatment in order to achieve improved physical and mental health outcomes. SISTAAH Talk includes women from across Miami-Dade and Broward counties, reaching an average of 20 women each month through education, outreach, and research. In 2013, SISTAAH Talk breast cancer survivors (N=240) participated in focus group discussions and completed lifestyle assessments for the National Institute of Minority Health & Health Disparities-funded pilot study, Assessing Lifestyle Modification Needs & Experiences of African American Women [13]. Four focus group discussions (n=42; mean age 45.73 years, SD 7.91, range 35-75 years) identified barriers to and intervention approaches for enhancing dietary intake and PA. Themes emerging from content analysis converged into the following categories: practical tools (goal setting, self-monitoring), talk as central, led by BCSs, support group approach, “hands-on” or interactive nutrition (cooking) and physical activity education, and community-based (not community placed) research. The findings of these focus group discussions will be combined with theories in an intervention planning process between investigators and BCSs to inform the design of mCPA.

SISTAAH Talk members (n=12), treated for >1 year for Stages I-IIIc breast cancer, 75 years of age or younger, and English speaking/writing, were identified by leaders of the support group as good role models to participate in developing mCPA. Each applicant was interviewed by the principal investigator and support group facilitator to determine comfort level in participating in focus group discussions, key informant interviews, and app content development (eg, videotaping cooking demonstrations and PA).

### Participatory Engagement

SISTAAH Talk members participating in mCPA reviewed themes from focus group discussions during three telephone support group meetings with the principal investigator. To describe the participatory process of app development, Table 1 outlines contributions for each element used in the process.

**Table 1 table1:** Participatory process of app development.

Element	Participant contribution	Investigator contribution	Outcome
Theoretical framework	Consider importance of lifestyle change to everyday life and survival	Identified theory to undergird BCSs’ belief that eating healthy and exercising regularly impacts survival	Health Belief Model; Theory of Planned Behavior
Peer-led activities	Include SISTAAH Talk members in all activities	BCSs as equal partners (facilitators, discussants) of cooking demonstrations, PA sessions, and focus group discussions	12 BCSs selected by SISTAAH Talk facilitator and mCPA principal investigator
Hands-on experiences	Mirror SISTAAH Talk activities by featuring BCSs cooking and exercising	Experiential nutrition and PA education	YouTube videos
Dietary intake	Feature recipes developed by AA community members; include practical, achievable recommendations that avoid drastic changes	Strategies and recipes promoting Cancer Prevention Guidelines	Down Home Healthy Living Cookbook
Physical activity	Walking, yoga, and strength training; advice from a BCS; consider different body sizes and practical, achievable goals	Symptoms such as lymphedema (swelling in an arm), arthralgia (pain in a joint), and neuropathy (numbness or weakness)	BCS-led walking, yoga, and strength training PA
Talk as central	The SISTAAH Talk approach to discussing lifestyle change	Incorporate beliefs, benefits, and barriers to lifestyle change as an instructional tool	Didactic sessions for goals, monitoring progress, and providing/receiving feedback

### Theoretical Framework

To provide a conceptual basis to undergird mCPA content, we will use the (1) health belief model (HBM) and (2) theory of planned behavior (TPB) (see Table 2). The HBM suggests that health-related cognitions for determining behavior considers the breast cancer survivor’s *belief* that lifestyle behaviors affect breast cancer recurrence, how *severe* the recurrence would be, and the *cost/benefits* of lifestyle change [22]. The TPB posits that health behavior is affected by past breast cancer experience and social norms (ie, lifestyle practices) more so than beliefs (ie, a link between breast cancer recurrence and lifestyle) [23].

**Table 2 table2:** Theoretical framework by mCPA construct.

	Health Belief Model^a^			Theory of Planned Behavior^b^	
Component	HBM1	HBM2	HBM3	TPB4	TPB5
Education	×	×	×		
Instructions			×		
Goal setting					×
Social support				×	
Provide feedback					×
Prompt review					×
Self-monitoring		×			×
Teach use of cues		×			
Action planning				×	

^a^Health Belief Model: HBM1 (perceived costs); HBM2 (health benefits); HBM3 (cues for action).

^b^Theory of Planned Behavior: TPB4 (subjective norms/social support); TPB5 (behavior control).

### Cancer Prevention Guidelines and App Content

The proposed app will focus on the AICR guidelines for cancer survivors [7]: (1) Be as lean as possible without becoming underweight, (2) Be physically active for at least 30 minutes every day to help prevent cancer and prevent recurrence of cancer, (3) Avoid sugary drinks and limit consumption of energy-dense foods (particularly processed foods high in added sugar, low in fiber, or high in fat), (4) Eat more of a variety of vegetables, fruits, whole grains, and legumes such as beans, taking up at least 2/3 of your plate, (5) Limit consumption of red meats (such as beef, pork, and lamb) and avoid processed meats, taking up only 1/3 or less of the space on your plate, (6) If consumed at all, limit alcoholic drinks to two for men and one for women a day, and (7) Limit consumption of salty foods and foods processed with salt (sodium) by substituting herbs and spices high in phytochemicals (eg, basil, turmeric, paprika, thyme, and dill).

mCPA will include a flexible and autonomous approach to changing eating and PA behaviors. Tools on the app to support the development of self-regulatory skills and successful lifestyle change strategies will feature a range of instruments (eg, informational and self-monitoring) designed to enhance users’ awareness of and motivation to work toward cancer prevention guidelines. For example, informational tools will include options to view individual goals and plans and to access selected strategies (eg, eating out, planning meals, incorporating PA through the day). Self-monitoring tools will include options to receive personalized feedback on progress and access to support through links to social media (eg, Facebook, twitter). App users will establish dietary intake and PA goals, access strategies to support these goals, develop plans of how to meet them, review progress, and receive feedback on goal achievement. Employing a support group format, users will access cooking demonstrations, exercise instructions, and practical advice through links to YouTube videos.

A community-engaged process for transforming main dishes, side dishes, snacks, and desserts into healthier options and for presenting advice on dietary intake and physical activity for cancer prevention has been previously described [24]. Dishes from the cookbook with lifestyle tips, entitled, “Down Home Healthy Living (DHHL) 2.0,” [25] will be featured on the app. The purpose of the cookbook is to promote awareness of cancer prevention guidelines in African American communities. For the DHHL 2.0 cookbook with lifestyle tips, recipes were solicited from the National Black Leadership Initiative on Cancer community coalitions and dietary intake advice from participants in the Educational Program to Increase Colorectal Cancer Screening (EPICS). With guidance from a chef and registered dietitian, recipes were tested, assessed, and transformed. Lifestyle advice was obtained from focus groups. The cookbook has been distributed in print form to 2500 EPICS participants and shared electronically through 25 websites.

Physical activities for the app, specifically, walking, yoga, and strength training, were selected by SISTAAH Talk members during focus group discussions as options for inclusion in an intervention. A SISTAAH Talk member, BCS, and certified, licensed, insured fitness instructor will lead the PA experiential and instructional videos.

### Mobile Cancer Prevention App Development

A timeframe for developing the app is included in Table 3. The initial step in developing the app was establishment of a research protocol. SISTAAH Talk members met with investigators via telephone conference call August-September 2015 to complete the research protocol for obtaining Institution Review Board (IRB) approval, which was granted in October 2015. The Georgia Regents University IRB approved this research plan. Informed consent will be obtained from all participants.

During August-September 2015, content and format for the app was also outlined. SISTAAH Talk members will be videotaped during cooking and PA demonstrations at three time points (December 2015, January and February 2016). A prototype of the app will be developed, presented, revised, and tested during the final 6 months of the study (May-October 2016).

**Table 3 table3:** App development timeline.

Steps	Oct. 2015	Dec. 2015	Jan. 2016	Feb. 2016	Mar. 2016	Apr. 2016	May 2016	June 2016	July 2016	Aug. 2016	Sept. 2016	Oct. 2016
Obtain IRB approval	✓											
Outline app content	✓											
Conduct focus groups		✓	✓	✓								
Tape cooking demos		✓	✓	✓								
Tape PA demos		✓	✓	✓								
Analyze focus group data					✓	✓	✓					
Conduct key informant interviews		✓	✓	✓								
Analyze key informant interview data					✓	✓	✓					
Develop app prototype								✓	✓			
Pretest draft app										✓		
Finalize app											✓	
Publish manuscripts				✓				✓				✓
Submit research proposals												✓

The proposed Web-based app will run like a Web page, with the app operating on an external server and the user accessing the app through the Web browser from a smartphone. The app will be developed and prototype-tested prior to going live on the smartphone. Participants will be provided a link to the app, which will transition from gray to color, with a pop-up message indicating that a component is now available for feasibility testing. Figure 1 provides a sample of the smartphone app interface.

Following informed consent, participants will engage in four activities to develop the content of the app. Each activity will be audio- and videotaped, with edited versions serving as content for mCPA. The first activity, didactic instructions, will provide information on goals for, benefits of, and strategies for enhancing dietary intake and PA. Researchers will present evidence linking lifestyle to breast cancer incidence and recurrence, review AICR guidelines for cancer survivors, and provide strategies for adhering to these guidelines, and address questions and concerns of the participants. Next, through interaction with investigators and other support group members, participants will develop app features for setting individual SMART (specific, measurable, actionable, realistic, time-sensitive) goals, monitoring progress, and providing/receiving feedback. Experiential nutrition education, with hands-on activities, including recipe development, modification, and taste testing through interactive cooking demonstrations, will be captured for the app. Finally, participants will engage in interactive PA, including walking at various levels (eg, power, speed interval, walking-to-jogging, and stretching), yoga (eg, physical postures, conscious breathing, and meditation), and strength training (eg, slowly progressive lifting of lightweight dumbbells) though a series of 30-minute sessions.

Focus group discussions and key informant interviews will be conducted to obtain participants’ feedback about app usefulness, identify the need for new system features and design requirements, and measure the acceptance of the mobile app and its features. Questions have been developed for the focus group discussions and key informant interviews based on the health belief model and theory of planned behavior (see Multimedia Appendix 1).

Four 90-minute focus groups with 12 SISTAAH Talk members and led by investigators, will explore three factors: performance expectancy, effort expectancy, and participant-centered factors. Performance expectance is defined as the degree to which a BCS believes that using the app will help attain lifestyle goals. Effort expectancy is the degree of ease associated with use of the app. Participant-centered factors include developing an app that is respectful of and responsive to user preferences, needs, and values, and ensuring that BCSs guide the development process. Acceptability will be determined by attitudes towards technology, anxiety, self-efficacy, and behavioral intention (eg, intent to use the app). Usability will be measured based on facilitating conditions and user-friendliness.

Three key informant interviews for each participant (n=36) will be conducted to ensure that perspectives across mCPA users are captured. Participants will be charged at baseline, midway, and postdevelopment with reviewing the app to make suggestions for adaptations and refinements and determine acceptability. Key informants will be provided access to the app, as it is being developed, and asked for feedback as part of a telephone follow-up.

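### Table 3 places all 36 key informant interviews three to four months before prototype work starts, so the postdevelopment round cannot take place as the text describes

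*Protocol article*

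**What the plan says.** The section Mobile Cancer Prevention App Development gives two accounts of when participants review the app.

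**The text.** Each of the 12 participants has three key informant interviews, 36 in all. The next sentence sets three review points: "Participants will be charged at baseline, midway, and postdevelopment with reviewing the app to make suggestions for adaptations and refinements and determine acceptability". Informants are to have access while the app is being built and to give feedback by telephone. The focus groups and interviews together are meant to measure acceptance of the app and to identify needed features. One of the focus group factors is ease of use: "Effort expectancy is the degree of ease associated with use of the app". The same section dates the prototype work: "A prototype of the app will be developed, presented, revised, and tested during the final 6 months of the study (May-October 2016".

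**Table 3.** The rows "Conduct key informant interviews" and "Conduct focus groups" are ticked in December 2015, January 2016 and February 2016 only. The row "Analyze key informant interview data" is ticked in March to May 2016. The row "Develop app prototype" is ticked in June and July, and "Pretest draft app" in August. Finalisation is in September.

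The Data Collection section adds that the first iteration goes to a discussion forum once the coded themes have been applied. Acceptability, as intention to use, is judged there.

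**The concern.** A postdevelopment review needs a developed app. The only interview dates in the article come before any prototype, and the analysis of the interviews is ticked no later than May 2016. A team that followed Table 3 would finish interviewing without anyone having used the app.

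What is at stake is the meaning of the reported results. User-friendliness, and acceptability after development, are properties of something people have handled. Answers collected in December to February would describe expectations of a concept. If they were later reported as usability or acceptability of the app, they would misstate the evidence for taking it into the intervention testing planned for early 2017.

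**Working it through.** No sample-size or power formula applies. The check is a count of interviews and a comparison of dates.

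**Step 1: reproduce the stated number of interviews.** 12 participants × 3 interviews = 36, which agrees with the article. One round is 36 / 3 = 12 interviews.

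**Step 2: read the dates from Table 3.** Each row checked has 12 month cells, so the ticks line up with the column heads.

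| Step | Months ticked |
|---|---|
| Key informant interviews | Dec 2015, Jan 2016, Feb 2016 |
| Focus groups | Dec 2015, Jan 2016, Feb 2016 |
| Analysis of both | Mar, Apr, May 2016 |
| Prototype build | June, July 2016 |
| Pretest | Aug 2016 |
| Finalisation | Sept 2016 |

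**Step 3: gaps from the last interview month (February, month 2 of 2016).**

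- To the start of prototype work on the text (May): 5 − 2 = 3 months.
- To the start of the build in Table 3 (June): 6 − 2 = 4 months.
- To the end of the build (July): 7 − 2 = 5 months.
- To finalisation (September): 9 − 2 = 7 months.

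The text and the table differ by a month on when prototype work starts. The conflict holds under either date.

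**Step 4: apply the gaps to the three review points.**

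- *Baseline (12 interviews).* An early discussion of content and intended features fits December to February.
- *Midway (12 interviews).* At most, participants could see mock-ups or early components. The article shows a sample interface and says that components are released one at a time through a link, so some material might exist. No built app does.
- *Postdevelopment (12 interviews).* Not possible as described, because the latest ticked month precedes the build under both dates.

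**Step 5: check whether a misplaced tick explains it.** The interview analysis row follows the interview row directly and ends in May, before the build starts in Table 3. The Data Collection section also puts coding and themes before the first iteration. The early placement is therefore consistent across the article. It is the later review points that have no place in the timeline.

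**The case against.** Four points can be made on the other side.

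1. *The app is assessed elsewhere.* This stands. Table 3 has an August pretest. The Data Collection section has a forum, which includes the study participants, where the app itself is shown and a second iteration follows from the comments. A reader might infer that the study cannot test its own hypothesis. The documents do not support that. In addition, the Introduction defines acceptability as frequency and duration of usage, which the items listed for the focus groups and interviews do not measure, so moving interviews would not supply that measure either.

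2. *The focus groups belong before the prototype.* Largely true. Their factors are mostly expectancies and participant preferences, they also serve to identify design requirements, and themes are needed before the first iteration. Nothing says that they are held with a prototype in hand. A reader might count all four as misplaced, but the documents do not support that. What remains is narrower: any user-friendliness data from them would be anticipatory.

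3. *The telephone follow-up may be separate from the interviews in Table 3.* The text does not rule this out. However, three interviews match three review points in adjoining sentences, and a separate activity would still have no row in the timeline.

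4. *It is uncertain how many interviews need the app.* Fair. A reader might count midway and postdevelopment together as 24. Only the postdevelopment 12 are clearly impossible, since a midway review could use partial material.

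**Conclusion.** The text and Table 3 contradict each other on the timing of the interviews. If Table 3 is followed, the postdevelopment round (12 of 36 interviews) cannot take place as described, and the midway round is limited to mock-ups or early components. Interviewing ends 3 months (text) or 4 months (Table 3) before prototype work starts and 7 months before finalisation.

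This rests on two assumptions: that the three interviews are the three review points, and that Table 3 is the working schedule. If the first fails, the postdevelopment review is unscheduled rather than mis-scheduled. If the second fails, Table 3 is wrong and must be changed to match the text. Either way the section needs correction.

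The conclusion is confined to the interviews and to any ease-of-use data gathered before the app exists.

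**What to change.** Revise Table 3 and add one reporting rule to the text.

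- Keep the baseline interviews and the formative focus groups in December 2015 to February 2016, with analysis in March to May. These still supply the themes needed for the first iteration.
- Move the midway interviews to the prototype build, June and July 2016.
- Move the postdevelopment interviews to the August pretest. They then come after the build and before the September finalisation, so suggested refinements can still be used. October interviews would come too late for that.
- Add an interview-analysis tick in August to October 2016. This stays within the stated end of the study in October 2016.
- State that ease of use and acceptability of the app are reported only from contacts made with the app available, and label the December to February data as formative expectations.

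The cost is a second, compressed analysis period alongside finalisation. The number of contacts stays at 36 interviews and four focus groups, and the planned availability for testing in early 2017 need not move.

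If the dates cannot change, the text should instead describe these sessions as formative only and name the pretest and the forum as the sources of data on the app. That gives up the individual postdevelopment reviews.
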